## Abstract

**Background:**

Parkinson’s disease is a degenerative neurological condition causing multiple motor and non-motor symptoms that have a serious adverse effect on quality of life. Management is problematic due to the variable and fluctuating nature of symptoms, often hourly and daily. The PD_Manager mHealth platform aims to provide a continuous feed of data on symptoms to improve clinical understanding of the status of any individual patient and inform care planning. The objectives of this trial are to (1) assess patient (and family carer) perspectives of PD_Manager regarding comfort, acceptability and ease of use; (2) assess clinician views about the utility of the data generated by PD_Manager for clinical decision making and the acceptability of the system in clinical practice.

**Methods/design:**

This trial is an unblinded, parallel, two-group, randomised controlled pilot study. A total of 200 persons with Parkinson’s disease (Hoehn and Yahr stage 3, experiencing motor fluctuations at least 2 h per day), with primary family carers, in three countries (110 Rome, 50 Venice, Italy; 20 each in Ioannina, Greece and Surrey, England) will be recruited. Following informed consent, baseline information will be gathered, including the following: age, gender, education, attitudes to technology (patient and carer); time since Parkinson’s diagnosis, symptom status and comorbidities (patient only). Randomisation will assign participants (1:1 in each country), to PD_Manager vs control, stratifying by age (1 ≤ 70 : 1 > 70) and gender (60% M: 40% F). The PD_Manager system captures continuous data on motor symptoms, sleep, activity, speech quality and emotional state using wearable devices (wristband, insoles) and a smartphone (with apps) for storing and transmitting the information. Control group participants will be asked to keep a symptom diary covering the same elements as PD_Manager records. After a minimum of two weeks, each participant will attend a consultation with a specialist doctor for review of the data gathered (by either means), and changes to management will be initiated as indicated. Patients, carers and clinicians will be asked for feedback on the acceptability and utility of the data collection methods. The PD_Manager intervention, compared to a symptom diary, will be evaluated in a cost-consequences framework.

**Discussion:**

Information gathered will inform further development of the PD_Manager system and a larger effectiveness trial.

**Trial registration:**

ISRCTN Registry, ISRCTN17396879. Registered on 15 March 2017.

**Electronic supplementary material:**

The online version of this article (10.1186/s13063-018-2767-4) contains supplementary material, which is available to authorized users.

## Background

Parkinson’s disease is a degenerative neurological condition associated with a range of motor and non-motor symptoms which have a very serious effect on the quality of life of the people affected. The processes that lead to Parkinson’s, and to how it manifests in individuals, involve numerous variables and pathways, and the aetiology is still not fully understood. Hence, management of the condition is challenging; people with Parkinson’s differ significantly in their symptoms and severity, how their disease progresses, their responses to treatments and their risk of complications [1]. To optimise treatment, a personalised approach is therefore needed [2].

A particular characteristic of advanced Parkinson’s disease is the fluctuation of symptoms and on/off periods. The mainstay of management is a pharmacological regimen that becomes increasingly complex as the disease progresses. Clinicians often find it difficult to identify the appropriate combination of medications because the clinical examination is just a snapshot of the patient’s fluctuating state. To accurately titrate the doses, they therefore have to rely on reports by patients and carers during short and infrequent clinic appointments. Electronic and paper motor symptom diaries have been used to improve the information available to clinicians. Both forms of reporting have, however, been shown to have similar numbers of erroneous entries, and a need for detection using automatic wearable devices has been identified [3]. More continuous symptom evaluation and feedback to clinicians could provide the required accurate and reliable information, with the potential to improve treatment and outcomes. This is the rationale behind the development of the PD_Manager system. This mHealth platform aims to provide a continuous feed of data on symptoms to improve clinical understanding of the fluctuating status of any individual patient and to inform care planning in which different experts may be involved, as well as prescribing. Continuous quantitative monitoring of activities and medication-induced fluctuations using wearable devices has been found feasible and useful in prior studies [4, 5], including exercise interventions [6]. Research has also focussed on finding the optimal location for monitoring motor performance [7].

The whole PD_Manager project involves a consortium of partners from several European countries. The development of the PD_Manager platform has been informed by qualitative research (interviews and focus groups) which explored the views and attitudes of people with Parkinson’s, carers and health professionals on the use of the technology for symptom control. Researchers have worked with device developers to refine the technology and undertake proof of concept testing in a hospital setting in Italy and Greece. No adverse events were experienced, and the pilot trial reported in this paper represents the next step in the testing of the system. The processes of the PD_Manager system will be checked in a community setting, and its acceptability and utility in clinical practice will be explored. Unlike other ongoing tests of wearable sensors in Parkinson’s patients which are observational [8], the PD Manager pilot will use a randomised controlled design. The most common traditional way of gathering information on symptoms from patients is through patient diaries [9]. This pilot study will therefore use symptom diaries as a comparator to the automated and electronic PD_Manager system for informing patient care and treatment plans.

### Research questions

The research questions are the following:What is the utility of PD_Manager as an aid to clinical decision making (in terms of informing patient care and treatment plans)?How acceptable is PD_Manager to patients and carers?What would be the resource implications of the use of the PD_Manager platform in healthcare programmes from a provider’s perspective?

### Aims and objectives

The aim of the pilot study is to explore the acceptability and utility of the PD_Manager system to patients, carers and clinicians, in a community setting, compared to a symptom diary, to inform further developments and the design of a larger clinical trial which will assess effectiveness (patient and carer health outcomes).

The specific objectives of the pilot study are to:Assess patient perspectives of the PD_Manager mHealth platform regarding comfort, acceptability, ease of use and understanding of Parkinson’sAssess the views of clinicians about the PD_Manager mHealth platform, i.e. usefulness of the information provided for decision making regarding patient management; acceptability in clinical practice; confidence in reliability of the informationExplore the resource implications and costs of the PD_Manager system for patients/carers and providers and consider these in the light of potential outcome differences, compared to the symptom diary, in a cost-consequences framework.

## Methods/design

### Design

An unblinded, parallel, two-group randomised controlled pilot study will be conducted to assess the acceptability and utility of the PD_Manager system, compared to traditional practices of using a symptom diary, for the management of people with Parkinson’s disease. The trial will be undertaken in three countries (England, Greece and Italy). The protocol and all study documents were prepared in English and subsequently translated into Greek and Italian.

### Participants

A total of 200 people with Parkinson’s and their carers (recruited as dyads) will be enrolled into the study through clinical centres (110 Rome, 50 Venice, Italy; 20 each in Surrey, England and Ioannina, Greece).

The inclusion criteria for people with Parkinson’s are as follows: (1) diagnosis of idiopathic Parkinson’s disease according to the UK Brain Bank Criteria; (2) Hoehn and Yahr disease stage 3 or 4 in OFF state [10]; (3) presence of motor fluctuations with an average of at least 2 h of OFF state during the day; (4) availability of a live-in carer who is willing to take part in the study; (5) good understanding of local language (in order to be able to complete the research). The exclusion criteria for people with Parkinson’s are the following: (1) presence of severe cognitive impairment (Parkinson’s disease dementia); (2) comorbidities with stroke or other brain disease; (3) current involvement in other Parkinson’s research.

For the assessment of the clinical perspective, a minimum of ten neurologists/prescribing clinicians will be asked to participate (six in Italy, two each in England and Greece).

### Trial processes

The Standard Protocol Items: Recommendations for Interventional Trials (SPIRIT) checklist is provided as Additional file 1. Patient flow through the trial is shown schematically in Fig 1; the SPIRIT checklist is summarised in Fig 2. Data collection at each stage is shown in Table 1.

**Fig. 1 Fig1:**
[figure not shown]
SPIRIT figure of enrolment, interventions and follow-up assessments

**Fig. 2 Fig2:**
[figure not shown]
PD_Manager schematic diagram of trial process

**Table 1 Tab1:** Summary of data collection at each stage

Participant group		Data capture at each stage		
	Baseline	During intervention, PD_Manager group from devices	During intervention, control group symptom diaries	Post-intervention, 2 week follow-up
Patient	Age, gender, education, disease duration, disease stage (Hoehn and Yahr score), main symptoms (tremor, bradykinesia, rigidity, dyskinesia), more affected side, UPDRS scores, current medications, comorbidities, views on technology Outcomes: EQ-5D-5L; PDQ-8; NMSS	Motor symptoms (gait, freezing of gait, bradykinesia, hypokinesia, dyskinesia, exercise); non-motor symptoms (cognition, sleep, mood)	All symptom domains captured through the PD_Manager intervention were self reported in a motor diary [16] and a wellbeing map [17] including: on/off; speech; sleep challenges; cognitive issues; activities and physiotherapy	Interviews on acceptability and ease of use of PD_Manager or symptom diary; usefulness of the education section of PD_Manager Outcomes: EQ-5D-5L; PDQ-8 and NMSS Changes in management plan and referrals
Caregiver	Age, gender, education, views on technology	No information is collected from caregivers in the PD_Manager group	No information is collected from clinicians in the symptom diary group	Interviews on acceptability and ease of use of PD_Manager or symptom diary; usefulness of the education section of PD_Manager
	Outcome: Zarit Caregiver Burden Scale (using short version)			Outcome: Zarit Caregiver Burden Scale (using short version)
Clinician	Qualifications, current role, number of Parkinson’s patients/week, length of time in practice, views on technology	No information is collected from clinicians in the PD_Manager group	No information is collected from clinicians in the symptom diary group	Usefulness and value of the information gathered (PD_Manager and symptom diary) for influencing management decisions; changes in management, referrals made

*EQ-5D-5L* EuroQoL-5Dimenions-5Levels, generic health-related quality of life scale [18–20], *PDQ-8* Parkinson’s Disease Questionnaire-8, disease specific measure of health-related quality of life [21, 22], *NMSS* Non-Motor Symptoms Scale [23], *UPDRS* Unified Parkinson’s Disease Rating Scale [11]

#### Recruitment, consent and baseline data collection of patient/carer dyads

People with Parkinson’s and their live-in carers will be identified by the consultant neurologist at each centre during routine clinic appointments or following an inpatient episode and invited to take part in the study. Eligibility will be confirmed by the clinician through completion of an eligibility checklist (based on the inclusion and exclusion criteria). The consultant will explain the purpose of the study and provide an information sheet containing full details of the study (see Additional file 2). The dyads will be given time to consider and asked to contact the research team if they want further information or wish to participate. Those who volunteer will be given an appointment to attend the hospital to meet a research nurse, where consent will be taken (separately by the person with Parkinson’s and the carer — see Additional file 2) and baseline data collected (from records, interview and clinical examination). Participants will be given unique study identifiers to maintain anonymity.

Baseline data collected (see Table 1) for the person with Parkinson’s will include disease duration, disease rating — Unified Parkinson’s Disease Rating Scale (UPDRS) score [11], disease stage [10], side of onset, current symptoms (tremor, bradykinesia, rigidity, dyskinesia), more affected side, Parkinson’s medications, comorbidities and body mass index (BMI) calculated from ‘height and weight’. Age, gender, ethnicity, education level and comorbidities will be collected for both members of the dyad. In addition they will both be asked if they have a preference for either the PD_Manager system or the symptom diary and will be questioned regarding their attitudes and expectations for each approach (using the Technology Acceptance Model measure [12, 13] and the Global Attitude to Technology question [14]), as these attitudes may affect the views they will express after the trial.

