#### Recruitment of clinicians

Volunteers will be sought from amongst clinicians recruiting patients to the study. They will be provided with an information sheet (see Additional file 2) and asked to provide informed consent (see Additional file 2). Baseline information will be gathered using a short questionnaire covering qualifications, current role, number of Parkinson’s patients treated per week and length of time in practice. Participants will also be asked to complete selected items from the Technology Acceptance Model measure [12, 13] and the Global Attitude to Technology question [14].

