### Acceptability outcomes

Assessment of acceptability for patients and carers will be undertaken at the end of the 14-day intervention period immediately after the feedback consultation with the clinician. A private room in the clinic will be identified for this purpose. Views will be collected by interview. Those in the intervention group will be asked about the following: how comfortable the devices were and how easy they were to use (determined with the same wearability and usability questions used in earlier testing of devices [15]; how useful the feedback they received from PD_Manager was; their views on communications with their neurologist regarding the PD_Manager outputs. The usefulness of the education section will also be assessed. A separate questionnaire will be used for participants in the control group to gather their views about the ease, burden and usefulness of the symptom diary. Questionnaires can be obtained from the corresponding author.

Back end data from the PD_Manager system will be provided to the researchers to enable an analysis of compliance with use of the devices by members of the intervention group. These data will be used to indicate how much the patients/carers valued using the devices.

Face-to-face interviews will be conducted with each clinician to explore their views about the relative usability and acceptability of PD_Manager and the symptom diary, and the value they perceive they provided in generating information for clinical decision making. Feedback will be sought by means of a semi-structured interview schedule on perceived usefulness to patients, carers and professionals, and adaptability to usual working schedules. The treating clinicians will be asked to comment on the ease of interpreting the data generated by the devices and the symptom diary and the ease of using this data in changing the treatment and care management of participants, as well as their views on this means of communicating with participants. The interview schedule can be obtained from the corresponding author.

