The pilot study has been designed to avoid standard risks of bias wherever possible. Participants will be randomised to the intervention and control groups to protect against selection bias, and care has been taken to ensure both groups receive the same attention at all stages of the study. Attrition or non-compliance (with devices or symptom diaries) do not constitute an issue but rather are actions of interest in our analysis of acceptability. However, the nature of the intervention is such that clinicians cannot be blinded to the group allocations. Potential does exist for selective outcome reporting. Hence, we are gathering information on attitudes to technology at baseline from participants, carers and clinicians.

The pilot study will not evaluate effectiveness and cost effectiveness of the PD_Manager system, although such a trial may be warranted if feedback from this pilot is positive. Outcome measures that may be used in an effectiveness trial are being tested within the pilot, and the findings will provide a basis for sample size calculation for a definitive trial. Preliminary cost estimates will also be computed in the pilot study to provide initial indications about the value of gathering further evidence from a larger trial.

Data security and confidentiality are major issues in trials of this sort. Data Protection Directive 95/46/EC, on the protection of individuals with regard to the processing of personal data and on the free movement of such data, will be strictly followed. Data from devices will be transferred (as described earlier) and stored in a web-based cloud database (NoSQL Database -3Dnet) in anonymised and encrypted format as employed by Apple for iPhones (a FiWare cloud-based process). The servers storing the information in the cloud platform are based on Biotronics 3D’s 3DnetMedical platform in the UK in an ISO27001-accredited data centre located in London. They are operated in accordance with the Data Protection Act. No third parties can access data either from the devices or during transmission. Access to the database will be strictly controlled and will only be shared with researchers on the PD_Manager project. Administrators of the web-based cloud database will not have access to data. The full data management policy of the cloud administrators is available from the corresponding author.

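### Technology acceptance and preference are listed at baseline only, and the arms get different questionnaires afterwards, so the published schedule has no common post-use acceptance score

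*Protocol article*

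**What the plan says.** **At baseline.** The section on recruitment, consent and baseline data collection says of the patient and carer that "they will both be asked if they have a preference for either the PD_Manager system or the symptom diary". It adds that they "will be questioned regarding their attitudes and expectations for each approach (using the Technology Acceptance Model measure", together with a global question on attitude to technology. The reason given is "as these attitudes may affect the views they will express after the trial". For clinicians, the section on their recruitment says: "Participants will also be asked to complete selected items from the Technology Acceptance Model measure". No preference question is listed for clinicians.

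**After use.** For patients and carers, the follow-up column of Table 1 lists "Interviews on acceptability and ease of use of PD_Manager or symptom diary". Under 'Acceptability outcomes', comfort and ease of use in the PD_Manager arm are "determined with the same wearability and usability questions used in earlier testing of devices". Control participants get a separate questionnaire on how easy, burdensome and useful the diary was. Clinicians have a semi-structured interview comparing the two methods. The Technology Acceptance Model measure and the preference question are not mentioned at this stage.

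**Purpose and analysis.** The Discussion says, in response to a concern about bias, "Hence, we are gathering information on attitudes to technology at baseline from participants, carers and clinicians". The aim is acceptability and utility relative to a diary. The Analysis section says that the two groups will be compared on quantitative variables, which include acceptability and usability at follow-up, in a non-confirmatory way.

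**The concern.** A comparison of two arms on acceptability needs something measured in the same way in both arms. The Technology Acceptance Model measure is the one structured acceptance instrument that the article describes as asked about both approaches, and it is not listed at the point where the arms are to be compared. The post-use instruments that are listed differ by arm, so a difference between them mixes a difference in acceptance with a difference in questions.

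The second loss is smaller. The article itself expects prior attitudes to colour later views, in an unblinded trial. If the same items were repeated, each person would have a before and an after value. The pilot could then also report the correlation between the two, which would help in designing the larger trial that it is meant to inform.

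**Working it through.** The article states no figure on this point, so there is none to reproduce. The main check sets the schedule side by side.

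| Item | Baseline | After use |
|---|---|---|
| Technology views (Table 1), patients | listed | not listed |
| Technology views (Table 1), carers | listed | not listed |
| Technology views (Table 1), clinicians | listed | not listed |
| Preference, patients and carers (baseline section text) | asked | not listed |
| Preference, clinicians | not listed | not listed |
| EQ-5D-5L, PDQ-8, NMSS (patients); short Zarit (carers) | listed | listed |
| Post-use acceptability questions | – | different in the two arms |

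Technology views thus appear at baseline for 3 of 3 groups and at follow-up for 0 of 3. Table 1 shows repeated measures in both columns, so the one-column listing of technology views reads as a single measurement. The text sections agree with it.

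**What a repeat would give.** Inputs: 100 patients per arm (200 in total, 1:1, from the sample size and randomisation sections); scores in SD units; baseline to follow-up correlation r = 0.5 to 0.7, which is an assumption. The calculation assumes complete follow-up.

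- Arm difference, unadjusted: SE = √(2/100) = 0.141 SD.
- Arm difference, baseline-adjusted: SE = 0.141 × √(1 − r²). For r = 0.5 this is 0.141 × 0.866 = 0.122; for r = 0.7 it is 0.141 × 0.714 = 0.101. The reduction is 13% to 29%.
- Mean change within an arm, 95% half-width: 1.96 × √(2(1 − r)) / √100 = 0.196 (r = 0.5) and 0.152 (r = 0.7) SD.
- Clinicians, taking the planned minimum of ten: 2.262 × √(2(1 − r)) / √10 = 0.72 and 0.55 SD, which is useful only as description.
- Preference shift within an arm, for illustration only: if 20% moved away from and 10% moved towards the allocated method, the net shift is −10 points with half-width 1.96 × √((0.2 + 0.1 − 0.01)/100) = 0.106, or 10.6 points. The switching rates are assumed.

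The 13% to 29% reduction is measured against no adjustment at all. If baseline attitudes already correlate at r₀ with whatever follow-up score is used, the ratio of standard errors is √((1 − r²)/(1 − r₀²)). This is closer to 1 for any r₀ between 0 and r. The article gives no basis for r₀, so the net gain cannot be stated.

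**The case against.** **The article is a summary.** The follow-up questionnaires and the clinician interview schedule are not reproduced, and the SPIRIT figure is not shown. Table 1 is visibly incomplete: at baseline it omits preference, ethnicity, body mass index and side of onset, all of which the text collects. The Economic evaluation section takes patient and carer time from follow-up questionnaires, yet neither Table 1 nor 'Acceptability outcomes' lists that item. The Discussion says attitudes are gathered at baseline, not that they are gathered only then. This stands. A reader might infer that the trial cannot show whether experience changed acceptance, but the documents support only that no repeat is listed.

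**No objective is defeated.** The research questions, objectives and analysis concern acceptability after use. None promises within-person change. Baseline attitudes are recorded as a possible influence on later views, and one measurement before randomisation serves that purpose. This also stands, and it sets the severity. It does not answer the point about the arm comparison, which is part of the stated aim.

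**Prior attitude can already be handled.** A reader might infer that a favourable answer at two weeks could not be told apart from an attitude held at entry. That goes too far. Each patient's and carer's entry attitude and preference are known, so follow-up answers can be stratified by them or related to them. A covariate need not share the outcome's scale. Randomisation also protects the between-arm comparison from prior attitude.

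**The follow-up questions are about acceptance.** Ease of use, usefulness and comfort plainly belong to it, and the two questionnaires may share items. What is missing from the published text is a named common scale, not attention to the subject.

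**Clinicians.** They have no baseline preference to repeat, their experience is of reviewing data from both arms, and the interview already asks for a comparative view. For them only the selected items can be repeated, descriptively.

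**Conclusion.** As published, the schedule lists the Technology Acceptance Model items (patients, carers, clinicians) and the preference question (patients and carers) before use only, and it names different post-use acceptability questionnaires for the two arms. It therefore provides no common post-use acceptance score and no before-after comparison on one instrument. The severity is low: this is an inexpensive improvement to a comparison that the trial already intends, not a mistake in the plan.

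The chief benefit is the shared score itself. Precision comes second, and the standard errors given above rest on the assumed correlation and on 100 analysed patients per arm. It would be wrong to present the whole 13% to 29% reduction as what the present plan forgoes, because baseline attitudes are already available for adjustment. The conclusion falls away if the questionnaires that are not shown already repeat these items.

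**What to change.** Add to the follow-up column of Table 1 and to 'Acceptability outcomes', or state there if it is already planned:

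- **Patients and carers, two-week visit:** the same Technology Acceptance Model items as at baseline, answered for the allocated approach, and the same preference question.
- **Clinicians, at their interview:** the same selected items as at entry, reported descriptively only.
- **Reporting:** the arm difference in the common follow-up score, adjusted for the person's own baseline score; within each arm, descriptive change from baseline and preference before against after. If baseline is scored separately for each approach, enter both scores as covariates. The score for the allocated approach alone is a different quantity in each arm and is not balanced by randomisation.

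The existing wearability, usability and diary questions stay as they are. The cost is a few minutes per person at a visit or interview already scheduled, using items already in use at baseline, plus one extra table. The downside is slight additional questionnaire burden.
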